### Assessment of risk and difficulty factors

3.2

Risk factors affecting surgeon performance will be rated exclusively by surgeons, whereas those impacting the anaesthetist will be assessed solely by anaesthetists. Risk factors influencing both surgical and anaesthetic outcomes will be evaluated by both groups. Surgeons will assess parameters related to surgical difficulty and complication risk, while anaesthetists will focus on factors contributing to the risk of complications.

To enhance accessibility, the risk prediction index will primarily utilise routinely available preoperative patient characteristics and easily quantifiable intraoperative conditions. Each variable will be assigned a numerical value, with higher values indicating greater significance in determining outcomes.

As peri- and postoperative complications arise from both surgical and anaesthetic risk factors, input from both disciplines will be essential in developing the index.

To evaluate the association between proposed parameters and complications, and to estimate their likelihood, a nomogram will be constructed using data from the CAMUS Collaboration database, supplemented with parameters from a prospective open cystectomy database at the University of Bern. The likelihood of complications will be critical, as each parameter will be assigned a specific weight to be incorporated into the risk prediction score.

Institutional databases will be utilised to create a model predicting the impact of certain parameters on peri- and postoperative complications at 90 and 360 d after surgery. Additionally, organ-specific scoring systems for bladder, prostate, kidney, and testicular cancer will be developed using a nomogram and institutional databases.

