### Identification and description of factors

3.3

In the initial phase of the study, risk-predicting parameters will be defined using data from the CAMUS Collaboration cystectomy database, which will include pre- and intraoperative variables sourced from 178 centres worldwide. Additional parameters from a prospective open cystectomy database maintained by the Urology Department at the University of Bern will further enhance data collection. The difficulty estimation score will be developed and validated using these data, supplemented by prospectively collected parameters detailed in round 1 of the study.

The RC cohort will be selected as the primary focus due to its high complication rate and clinical relevance. In subsequent phases, the scoring system’s performance will be assessed in various patient cohorts who have undergone RP, PN, radical nephrectomy (RN), radical nephroureterectomy (RNU), and retroperitoneal lymph node dissection (RPLND).

The first Delphi round will involve expert consensus to identify parameters influencing peri- and postoperative morbidity, mortality, and surgical difficulty. For example, parameters relevant to RP will be outlined in Supplementary Tables 1 and 2. Experts will be guided by the results derived from nomograms. Organ-specific factors, as part of the organ-specific scoring system, will also be examined for procedures such as RC, RP, PN, RN, RNU, and RPLND, with further details provided in Supplementary Table 3.

To assess the impact of these parameters on both difficulty and risk, a comprehensive description of the associated conditions and characteristics will be required. These parameters will be categorised according to a five-level scale of difficulty: easiest, intermediate easy, standard, intermediate difficult, and most difficult. For instance, preoperative BMI ranges will be classified as follows: BMI 18–22 kg/m^2^ will correspond to the easiest grade, while BMI >40 kg/m^2^ will be categorised as most difficult. Similarly, for organ-specific factors such as prostate size in RP, a prostate volume of 20–30 cc on magnetic resonance imaging will represent the easiest level of difficulty, whereas a volume exceeding 200 cc will be classified as most difficult.

Notably, multiple conditions may be associated with the same level of difficulty. For example, multiple prior open procedures or laparoscopic surgeries involving mesh insertion may be considered of intermediate difficulty.

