For inclusion in the initial patient cohort (cohort 1), all patients who underwent open or minimally invasive RC and urinary diversion between 2000 and 2021 were selected. Cohort 2 includes all patients who underwent open or minimally invasive RP between 2000 and 2020. Cohort 3 comprises all patients who underwent PN, RN, RNU, and RPLND. All variables from the CAMUS database have been included in the analysis.

Certain variables were adjusted for analytical purposes, such as categorising renal function into grades 1–5 and grouping intervention events (eg, intensive care treatment) into broader categories with subgroups (eg, cardiac and pulmonary intensive care). These adjustments were made to establish preoperative comorbidity categories and transform non-normally distributed variables. The primary study outcomes are the CDC/CAMUS grade or death within 90 d and the Comprehensive Complication Index (CCI).

Preoperative (expected/known) risk and difficulty factors used to calculate patient-specific risks and surgical difficulty were selected a priori based on their predictive value, routine availability to the surgeon before the operation, and clinical face validity. Similarly, intraoperative (unexpected/unknown) risk and difficulty factors were selected based on their predictive value, the surgeon’s expertise, and clinical validity. Immediate postoperative factors that refine risk estimation follow the same methodology.

All preoperative, intraoperative, and immediate postoperative factors will be evaluated using the Delphi method, as described previously.

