Logistic regression will be used to examine the relationship between major complications/death, and the risk index score (treated as an ordered categorical variable based on predefined categories) and its components across the three patient cohorts. Model discrimination will be assessed by calculating c-statistics (area under the receiver operating characteristic curve). For model calibration, the Hosmer-Lemeshow (HL) goodness-of-fit test will be used to compare predicted versus observed outcomes between the two cystectomy cohorts. In the final cohort, differences in complication rates across individual scores will be compared using chi-square tests. Additionally, using morbidity (complicated/uncomplicated) and mortality (dead/alive) as dichotomous dependent variables, multiple logistic regression models will be derived. Overall model significance will be assessed via the model chi-square statistic, and differences between observed and expected outcomes will be evaluated using the HL test.

To develop the surgical difficulty index, pre-, intra-, and postoperative parameters and outcome measures will be determined by experienced high-volume surgeons (≥1000 major interventions and >10 yr of surgical experience) using the Delphi method. Pre- and perioperative parameters that potentially increase operative difficulty and risk will be assessed using a 5-point scale, as shown in Supplementary Tables 1–3. Primary outcome measures for surgical difficulty will include operation duration, blood loss and transfusion, use of haemostatic agents, and the surgeon’s judgement (on a scale from 0 to 100).

The performance of the universal surgical risk calculator, which includes multiple specialities and hundreds of procedures, will be compared with the performance of our risk calculators, specifically programmed for this score development. This comparison will be made for individual procedures (eg, RC and RP).

Alternatively, to create risk prediction models, random-intercept, fixed-slope hierarchical models (using SAS GLIMMIX) will be employed. These models account for case clustering within hospitals and impose an empirical Bayes-type shrinkage adjustment. As a result, both universal and procedure-specific surgical risk calculators will be developed. The performance of the universal versus procedure-specific models will be evaluated using three metrics: the c-statistic, the HL statistic (in a revised graphical form), and the Brier score.

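### The risk score's calibration check is tied to two cystectomy cohorts where the plan defines one, and no predicted-versus-observed check of the score is stated for prostatectomy or cohort 3

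*Protocol article*

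**What the plan says.** Section 3.7 (Data collection) of the protocol article sets out the cohorts. For cohort 1, "all patients who underwent open or minimally invasive RC and urinary diversion between 2000 and 2021 were selected". Then "Cohort 2 includes all patients who underwent open or minimally invasive RP between 2000 and 2020", and "Cohort 3 comprises all patients who underwent PN, RN, RNU, and RPLND".

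Section 4.1 turns regression coefficients into a 10- or 20-point score, with cut-offs rounded so that surgeons can remember them. It relates major complications or death to this score "and its components across the three patient cohorts", with the c-statistic for discrimination. For calibration, the Hosmer-Lemeshow (HL) "goodness-of-fit test will be used to compare predicted versus observed outcomes between the two cystectomy cohorts". For what it calls the final cohort, it plans chi-square tests of complication rates by score.

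Two cystectomy data sources are described. Section 3.3 starts from "data from the CAMUS Collaboration cystectomy database, which will include pre- and intraoperative variables sourced from 178 centres worldwide". Section 3.2 has the nomogram data "supplemented with parameters from a prospective open cystectomy database at the University of Bern", and section 3.7 gives the Bern database as n = 1550.

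Other calibration work is planned for the regression models:
- Section 4.1: HL for the morbidity and mortality models, and graphical HL and Brier score for universal versus procedure-specific models.
- Section 4.2: C-index, HL and Brier score of the generic model against surgery-specific models for radical cystectomy (RC), radical prostatectomy (RP) and partial nephrectomy (PN).
- Section 4.3: HL and Brier score in a random one-third validation set.

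**The concern.** The population named for calibrating the score does not match the plan's own cohorts. An analyst following the text cannot tell which two datasets to use, and nothing in it directs a calibration check of the score in cohorts 2 and 3, although the score is to be studied there.

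This matters because the score is developed first in cystectomy, chosen in section 3.3 for its high complication rate, and is then assessed in other operations. The tool is also meant for patient counselling (section 5.1.2), where the absolute level of risk counts. A c-statistic depends only on ranking. A chi-square test across score groups asks whether rates differ between groups. Neither compares predicted with observed risk, so neither can show that a score which ranks patients well predicts the wrong level.

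**Working it through.** The plan gives no figure to reproduce here. The check is a count of cohorts and a trace of every calibration step, followed by one illustration on assumed inputs.

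**1. Cohort count.** Section 3.7: cohort 1 = RC; cohort 2 = RP; cohort 3 = PN, radical nephrectomy (RN), nephroureterectomy (RNU) and retroperitoneal lymph node dissection (RPLND). Cystectomy cohorts: 1 of 3. Section 4.1 needs 2. Two cystectomy cohorts plus a final cohort make 2 + 1 = 3, which matches the number of cohorts but not their definition: prostatectomy then has no place.

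**2. The two-database reading.** CAMUS cystectomy and Bern make two sources. Sections 3.2, 3.3 and 3.7 use both for development, and none says that either is held out. A check in them is then apparent calibration, and cohorts 2 and 3 are still outside it.

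**3. Stated calibration checks, by object and operation.**

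| Operation | Points score | Regression models, by procedure (section 4.2) |
|---|---|---|
| RC | HL, section 4.1 (datasets unclear) | HL, Brier |
| RP | none stated | HL, Brier |
| PN | none stated (chi-square of rates only, if the final cohort is cohort 3) | HL, Brier |
| RN, RNU, RPLND | none stated (same) | none stated |

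The section 4.1 HL tests of the morbidity and mortality models are not limited to cystectomy, but no breakdown by operation is given. The section 4.3 split is random, so both parts have about the same mix of operations, and no breakdown is given there either.

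**4. Score versus model.** The score is built by weighting, banding and rounding the regression terms. Those steps change the predictions, so good calibration of the regression does not establish good calibration of the score.

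**5. What a within-procedure check would show (illustration).** Assumptions, none from the article: predicted logit = -0.95 + 0.8x with x standard normal, giving a mean predicted risk of about 30%; true logit = predicted logit + ln(k); 500 runs per setting; 10 groups; 5% level. The statistic is the sum over groups of (O - E)^2 / [E(1 - E/n_g)], where n_g is the group size, referred to chi-square with 10 degrees of freedom.

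| k (true odds / predicted odds) | Mean predicted | Mean observed | c-statistic | HL rejects at n = 500 / 1000 / 1500 |
|---|---|---|---|---|
| 1.0 | 30% | 30% | 0.70 | 4% / 5% / 4% |
| 0.75 | 30% | 25% | 0.70 | 30% / 71% / 94% |
| 0.5 | 30% | 19% | 0.71 | 99% / 100% / 100% |
| 0.25 | 30% | 11% | 0.71 | 100% / 100% / 100% |

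The c-statistic hardly moves while the risk level goes wrong. A predicted-versus-observed test within the procedure finds a halving of the odds almost always, and a shift to 0.75 often, depending on n. So the choice of check decides whether such an error is seen.

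**The case against.** The strongest reply is that calibration outside cystectomy is planned. Section 4.2 compares HL and Brier results of the generic and surgery-specific models in RC, RP and PN, and sections 4.1 and 4.3 add further HL and Brier analyses. By the illustration above, a gross error of the generic model in RP or PN would probably show there. This stands, and it limits the point to the score itself and to RN, RNU and RPLND.

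Second, two cystectomy databases exist and are the likeliest meaning of the phrase. That is fair as a guess, but the article does not say it, and it leaves cohorts 2 and 3 without a score-level check.

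Third, a reader might infer that a check in the two development databases is empty because predicted and observed means must agree. They need not. Maximum likelihood with an intercept guarantees agreement only in the pooled development data, not within each database unless a database term is fitted, and not after rounding to points. The check is informative, but it remains apparent calibration.

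Fourth, calibration detail may sit in an analysis plan that is not shown. Section 3.3 also defers assessment in the other operations to later phases, and section 4.4 foresees external validation; neither names a calibration measure. Leaving out detail would be no fault. Here, however, the article states a population for the check, and that population conflicts with its own cohort definitions.

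**Conclusion.** The point holds in a limited form and should be corrected. The phrase naming the calibration cohorts is undefined against section 3.7 (one cystectomy cohort, not two). As written, the points score has no stated predicted-versus-observed check in cohorts 2 and 3, and three operations (RN, RNU, RPLND) have no procedure-level calibration check of any model. If the CAMUS and Bern databases are meant, the cystectomy check is apparent calibration unless one of them was held out.

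A reader might go further and infer that calibration in prostatectomy and kidney surgery is untested, or that gross miscalibration would pass unseen. The article does not support that, because section 4.2 covers the regression models in RP and PN. Nor can a multiple be put on the possible error: the article gives no event rates by operation and does not say that a cystectomy intercept is carried to other operations, so any such multiple would only be a ratio of assumed rates. The simulated figures show what each kind of test can detect under the stated assumptions; they do not estimate how well this score will calibrate.

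**What to change.** In section 4.1, replace the restriction to two cystectomy cohorts with predicted versus observed risk of the points score in each of cohorts 1, 2 and 3: calibration-in-the-large, calibration slope and a plot, by operation within cohort 3 where numbers allow. Keep the chi-square comparison as a description only.

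If CAMUS versus Bern cystectomy is intended, say so and state which set, if any, was not used to build the score. If both were used, label the result as apparent calibration.

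The cost is a change of wording and a few more plots on data already held. The reported calibration may look less favourable.

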### Data collection

3.7

The CAMUS Collaboration has established four independent outcome databases for patients undergoing open or minimally invasive RC, RP, PN, RN, RNU, and RPLND, This collaborative study has collected various pre-, intra-, and postoperative outcome variables, along with complication data (including complication type, intervention, and grading), to evaluate their potential as predictors for intra- and perioperative risk estimation. Additionally, a comprehensive single-centre cystectomy database from the University Hospital Bern (*n* = 1550) is included. In more detail, the CAMUS database includes a diverse patient population from various centres, reflecting a wide range of clinical scenarios and surgical outcomes. To minimise the potential selection bias, the exclusion criteria were restricted to patients with ≤10% missing data and by age factor, allowing the inclusion of all patients aged 18 yr and older. This approach ensures a representative cohort and enhances the generalisability of our results.

The required sample size was estimated using a power-based method for logistic regression models, considering the number of predictor variables ranging from 10 to 30 (refer to section 6.1 for more information). The calculations were performed using the pwr package [1] in the statistics software R, version 4.4.2 [2], utilising effect sizes based on assumed odds ratios of 1.2 (weak effect), 1.5 (moderate effect), and 2.0 (strong effect). The required sample size is reached when a statistical power of at least 80% is achieved at an alpha level of 0.05. To enable internal validation (see section 6.3), the final sample size was increased by 50%, ensuring sufficient data for both model training and validation. Consequently, the most extreme case—30 predictors with a weak effect size (odds ratio = 1.2)—required a sample size of 1180, which is well below the available sample size.

Patients eligible for inclusion are aged 18 yr or older.

Data collection has been conducted by trained and audited registrars, consultants, and study nurses at each participating hospital, ensuring standardised data definitions across all institutions. Missing data have been managed using imputation, specifically employing the Buck’s method. Patients with missing values for critical variables—such as the date of postoperative complication-intervention events, Clavien-Dindo complication (CDC) grade, or death within 90 d—have been excluded from the analysis.

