### Statistical analysis and development of the score

4.1

All statistical analyses will be conducted using R packages. Initially, a univariate analysis will be performed to examine the relationship between each pre- and intraoperative variable in the database and the primary outcomes. Variables with *p* ≤ 0.20 and ≤10% missing data will be considered for inclusion in a multivariable model, to ensure sensitivity and prevent the exclusion of potentially relevant factors. Among collinear variables, selection will be based on *p* values and their potential use in constructing an outcome score.

In the multivariable analysis, intraoperative variables will be entered independently and in combination with preoperative variables into a logistic regression model. Both forward and backward stepwise selection procedures will be employed (with entry criteria *p* ≤ 0.10 and inclusion criteria *p* ≤ 0.05) for outcomes of interest. The final model will be selected based on the Akaike Information Criterion (AIC). Variables that independently predict major complications or death will be considered as candidates for the risk index score. Alternative combinations of variables for the risk index score will be compared, emphasising simplicity, clinical safety, and predictive power.

After determining the final variables for inclusion, the magnitude of the β coefficients from the regression equation will be used to assign weights to each variable. Depending on the number of variables included, the score will be represented as either a 10-point or a 20-point scale. The intervals and cut-offs for each point level will be designed to ensure that a 1-point increase in the score corresponds to a proportional increase in the odds of a complication. The values for each cut-off will then be rounded to clinically relevant figures that can be recalled easily by surgeons. For instance, operation duration will be valued as follows: 0 points for ≤120 min, 1 point for 120–180 min, etc.

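### The chi-square comparison of complication rates across the ordered score does not check the per-point odds gradient the score is built to have; name a trend test and report the odds ratio per point

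*Protocol article*

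**What the plan says.** All the relevant text is in section 4.1 of the protocol article (Statistical analysis and development of the score).

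- Scale: after weights are taken from the regression coefficients, "the score will be represented as either a 10-point or a 20-point scale".
- Design property: intervals and cut-offs are chosen so that "a 1-point increase in the score corresponds to a proportional increase in the odds of a complication". The cut-offs are afterwards rounded to figures that surgeons can remember.
- Regression: major complications or death are related by logistic regression, in all three cohorts, to "the risk index score (treated as an ordered categorical variable based on predefined categories"). Discrimination is measured by the c-statistic.
- Final cohort: "differences in complication rates across individual scores will be compared using chi-square tests". The variant of chi-square test is not stated, and neither is the size of this cohort.

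The power statement in section 3.7 (Data collection), "a statistical power of at least 80% is achieved at an alpha level of 0.05", concerns the regression models. No power, sample size or decision rule is attached to the chi-square comparison.

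**The concern.** The score's defining claim is a log-linear one: each extra point multiplies the odds of a complication by a constant factor. A Pearson chi-square test across 10 or 20 score levels asks only whether the rates are all equal. Its value is unchanged if the score labels are shuffled, so it can be significant when the rates do not rise with the score. It also yields no estimate of the effect of a point.

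Rounding the cut-offs is a step at which the intended proportionality can be lost, so the property should be checked on the finished score. As worded, the final-cohort comparison cannot do that. Where the gradient is modest, spreading it over many degrees of freedom also costs power.

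**Working it through.** **1. Which named analysis checks the property?**

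| Analysis in section 4.1 | Uses score order? | Checks constant odds ratio per point? |
|---|---|---|
| Chi-square across individual scores, final cohort | No, if Pearson | No |
| Logistic regression, score ordered categorical | In part, depending on coding | Could, but no per-point odds ratio or linearity test is named |
| c-statistic | Yes, as a ranking | No |

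**2. Is there a figure in the plan to reproduce?** Not for this comparison. The only sample-size figure, 1180 in section 3.7, belongs to the regression models with "assumed odds ratios of 1.2 (weak effect), 1.5 (moderate effect), and 2.0 (strong effect") per predictor. Nothing below depends on it.

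**3. Power at equal noncentrality.** Assumptions: an exactly linear trend and a two-sided alpha of 0.05. The trend test and the Pearson test then share the same noncentrality λ, and

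power = P(χ²(df, λ) > χ²(0.95, df)).

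For the 1-df trend test, 80% power needs λ = 7.85 and 90% needs λ = 10.51. A 10-point scale gives 9 or 10 df and a 20-point scale gives 19 or 20, depending on whether zero is a level. With the same λ:

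| Trend-test power | Pearson 4 df | 9 df | 10 df | 19 df | 20 df |
|---|---|---|---|---|---|
| 80% | 59.5% | 44.6% | 42.6% | 31.6% | 30.8% |
| 90% | 74.0% | 59.0% | 56.8% | 43.5% | 42.4% |

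The 4-df column is for a score collapsed to five categories. To reach 80% power, the Pearson test needs λ = 15.65 at 9 df and 20.96 at 20 df. That is 15.65/7.85 = 2.0 and 20.96/7.85 = 2.7 times the sample size of the trend test.

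These figures are conditional: they fix the trend-test power in advance, and the plan does not state that power.

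**4. Simulation at plausible sizes.** Assumptions, none given in the plan: log-linear odds, 20% event rate, binomial-shaped score distribution, 6000 runs per row. N = 1550 is the single-centre cystectomy database in section 3.7. N = 517 is one third of it (1550/3), as if only that database were split as in section 4.3. N = 200 stands for a small cohort.

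| Score | N | Odds ratio per point | Trend | Pearson |
|---|---|---|---|---|
| 0–10 | 1550 | 1.5 | 100% | 100% |
| 0–10 | 517 | 1.5 | 100% | 99.1% |
| 0–10 | 1550 | 1.2 | 99.2% | 90.2% |
| 0–10 | 517 | 1.2 | 72.8% | 39.5% |
| 0–10 | 1550 | 1.1 | 64.3% | 31.8% |
| 0–10 | 200 | 1.5 | 92.6% | 68.1% |
| 0–20 | 517 | 1.2 | 94.6% | 63.0% |
| 0–20 | 517 | 1.1 | 47.6% | 18.2% |

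The loss therefore runs from almost nothing to more than half, according to gradient, number of levels and cohort size. The mismatch shown in step 1 does not depend on sample size.

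**The case against.** Four points can fairly be made for the plan.

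- **The word unordered is not there.** The text says only chi-square tests, and a chi-square test for trend is one of these. An article may leave the variant to a fuller document. This stands as a limit on the claim. Even so, comparing differences across individual scores reads most naturally as a homogeneity test, and stating the variant would settle it.
- **The ordering is used elsewhere.** A reader might infer that the plan ignores the gradient altogether. It does not: the regression treats the score as ordered and the c-statistic uses the ranking. What remains is narrower. A ranking measure says nothing about constant odds per point, and the regression text names neither a per-point odds ratio nor a linearity test.
- **A reader might infer that the chi-square test loses about half the power.** The documents do not support that as a general figure. It requires an exact linear trend, about 10 levels and a trend test that itself has about 70–80% power. At an odds ratio per point of 1.5 and N of 517 or 1550, the loss is at most about one percentage point.
- **A trend test does not prove monotonicity either.** It detects an average slope. That is correct, and it is why the trend test should be paired with a test of departure from linearity.

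The comparison is also not named as primary, and performance is judged mainly by the c-statistic, Hosmer-Lemeshow analyses and the Brier score. That limits the importance of the point but does not remove it.

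**Conclusion.** The point holds as a minor, cost-free improvement. If the chi-square comparison is a homogeneity test, it does not use the score's order and cannot check the constant-odds-per-point property that section 4.1 builds in and that rounding may disturb. No other named analysis fully covers this.

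The conclusion rests on the natural reading of an unqualified test name. The size of any power loss rests on quantities the article does not give: the size of the final cohort, the distribution of scores, the event rate and the true gradient. It should not be summarised in one number. There is no basis for saying that a sample size or a primary conclusion is wrong.

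**What to change.** In section 4.1, replace the chi-square comparison, or specify it, as a 1-df trend test: either Cochran-Armitage or the score as a linear term in the logistic model. Report the odds ratio per point with its 95% confidence interval, using the score with its final rounded cut-offs. Test departure from linearity with a likelihood-ratio comparison of the linear and categorical codings. If all 11 levels of a 0–10 score are occupied, the 10 df divide into 1 for trend and 9 for departure. Keep a table of observed complication rates by score so that readers can see the shape.

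The change uses the same data and a model already planned, needs no extra patients, and amounts to a sentence of text and a few lines of analysis.
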